## Abstract

**Background:**

Men who have sex with men (MSM) constitute a risk group for sexual transmitted infections (STIs), including HIV. Despite counselling interventions, risk behaviour remains high. Syndemic theory holds that psychosocial problems often co-occur, interact and mutually reinforce each other, thereby increasing high risk behaviours and co-occurring diseases. Therefore, if co-occurring psychosocial problems were assessed and treated simultaneously, this might decrease high risk behaviour and disease.

**Method:**

An open label randomized controlled trial will be conducted among 150 MSM with high risk behaviour recruited from the STI clinic of Amsterdam. Inclusion criteria are: HIV negative MSM with two STI and/or PEP treatment in the last 24 months, or HIV positive MSM with one STI in the last 24 months. All participants get questionnaires on the following syndemic domains: ADHD, depression, anxiety disorder, alexithymia and sex- and drug addiction. Participants in the control group receive standard care: STI screenings every three months and motivational interviewing based counselling. Participants in the experimental group receive standard care plus feedback based on the results of the questionnaires. All participants can be referred to co-located mental health or addiction services.

The primary outcome is help seeking behaviour for mental health problems and/or drug use problems. The secondary outcomes are STI incidence and changes in sexual risk behaviour (i.e. condom use, number of anal sex partners, drug use during sex).

**Discussion:**

This study will provide information on syndemic domains among MSM who show high risk behaviour and on the effect of screening and referral on help seeking behaviour and health (behaviour) outcomes.

**Trial registration:**

Trial Registration at clinicaltrail.gov, identifier NCT02859935.

## Background

Men who have Sex with Men (MSM) constitute a risk group for Sexually Transmitted Infections (STI), including HIV. The STI positivity rate – chlamydia, gonorrhea, syphilis and hiv - among MSM attending the STI clinic in Amsterdam is around 18% among HIV-negative MSM and 30% among HIV-positive MSM [1]. Besides this high positivity rate, there is a high recurrence of infections in this group. More than 10% of the men who were diagnosed with an STI had a new infection within one year [1].

For MSM with a high STI risk we started a case holding cohort: the MS2 cohort. We included 107 HIV-negative and 95 HIV-positive MSM from January 2014 till April 2016 [2]. If screened 4 times a year, in 25% of each visit a new STI was found and more then 40% reported using methamphetamine, mephedrone and/or γ-Hydroxybutyric acid (GHB)/ γ-Butyrolactone (GBL) during sex [2]. Despite motivational interviewing and counseling, risk behaviour remains high.

A syndemic is two or more afflictions, interacting synergistically and contributing to an excess burden of disease. The syndemic theory holds that psychosocial problems frequently co-occur, interact and mutually reinforce each other, thereby increasing high risk behaviours and co-occurring diseases [3]. According to the syndemic theory that explains the increased risk on STI in MSM, he following domains can contribute to risk behaviour: drug use, mental health problems, stigma, past or present abuse, and discrimination [4]. Sex related drug use is high among MSM in our MS2 cohort [2], and sex-related drug use is associated with STI [5, 6], HIV [6] and high risk behaviour [7] In addition, MSM report elevated levels of mental health problems, including Attention Deficit Hyperactivity Disorder (ADHD), depressive episodes, obsessive-compulsive disorder and alcohol and drug dependence [8, 9]. If however, co-occurring psychosocial problems were assessed and treated, it might decrease high risk behaviours and co-occurring diseases.

To test this theory we developed the syndemic based intervention (syn.bas.in). The purpose of this open label, randomized controlled intervention at the STI outpatient clinic of Amsterdam is to answer the following question: does syndemic screening and indicated referral to co-located mental health and/or addiction treatment services result in increased help seeking behaviour, and decrease risk behaviour in MSM who are at high risk for STIs and HIV?

## Methods: participants, interventions and outcomes

### Study population

All participants of the MS2 cohort [2] will be invited to join the syn.bas.in study. Other participants will be recruited directly from the STI clinic of the public health center of Amsterdam. Previous studies in the Netherlands have shown that MSM with an STI or a PEP treatment are at high risk of acquiring an HIV infection [10, 11]. Most MSM with HIV have shown high risk behaviour in the past and STI positivity is generally higher then among HIV negative MSM [1]. We expect this intervention to have the most impact on those showing recent high risk behaviour, therefor we choose the following inclusion criteria.

#### Inclusion criteria

The inclusion criteria are MSM, 18 years or older, sufficient command of Dutch or English andfor HIV positive MSM at least one STI* in the last 12 months.for HIV negative MSM at least two STI* or a PEP treatment in the last 24 months.

(* i.e. urethral, pharyngeal or anal gonorrhoea; urethral, pharyngeal or anal chlamydia; lymfogranuloma venereum; syphilis; acute hepatitis B and/or C; and newly diagnosed HIV infection. Genital warts or genital herpes do not count as inclusion criteria).

#### Exclusion criteria

Men will be excluded if they speak insufficient Dutch or English, are not able to complete follow-up or otherwise deemed by clinic staff to be unsuited for participation.

### Study intervention

All participants will receive standard care, including STI screenings every three months and offered a motivational interviewing based counseling session. STI screenings include tests for syphilis, hepatitis B - if not documented vaccinated - hepatitis C, HIV, and anal, urethral and pharyngeal chlamydia and gonorrhea. Asymptomatic men will be screened using a fast track procedure - i.e. no physical examination and self-sampling. Symptomatic men - with suspected STI related signs and/or complaints - will get a full physical examination, including anoscopy. Treatment and contact tracing will be offered to those with a newly diagnosed infection. At the initiative of the participant (e.g. in case of STI related complaints) additional screening will be available.

After explanation of the study by a study healthcare provider and informed consent is obtained, participants will be randomized either to the intervention or the control group. After intake, and at the final visit of the study, all participants fill out a set of questionnaires. Questionnaires will be sent via email and represent various syndemic domains (Table 1).

**Table 1 Tab1:** Questionnaires on syndemic domains that will be used in the syn.bas.in study for referral of MSM showing high risk behaviour at the STI clinic of Amsterdam

Syndemic domain	Questionnaire	Cut off (range)
Sex addiction	Sexual Compulsivity Scale [15]	≥ 24 (10–40)
Alcohol/drug addiction	AUDIT[17] DUDIT [18]	AUDIT ≥8 (0–12) DUDIT ≥8 (0–40)
Anxiety	Hospital Anxiety Depression Scale [20]	≥8 (0–21)
Depression	Hospital Anxiety Depression Scale [20]	≥8 (0–21)
ADHD	Adult ADHD Self Report Scale [19]	≥4 (0–6)
Alexithymia	TAS-20 [22, 23]	≥52 (20–100)
Partner violence	Stall [13, 24]	/
Childhood sexual abuse	Stall [13, 24]	/
Discrimination	Stall [13, 24]	/

Participants in the intervention arm will be offered the questionnaires a second time before their subsequent three-monthly follow-up visit. During these subsequent visit the outcome of all questionnaires will be discussed to provide the participant in the intervention group a better insight in potential mental and/or addiction problem(s) that possibly contribute to risk behaviour. Via feedback and motivational interviewing the willingness to seek help will be evoked and monitored. All study healthcare providers receive training by mental health care providers to address these issues and are available for consultation in between visits, if necessary. If help is accepted, participants will be referred to a relevant mental health or addiction treatment service. Since co-located care may help to reduce barriers and improve health seeking behavior, intake consultations are available at the STI outpatient clinic of Amsterdam.

Participants in the control group receive standard STI screening and motivational interviewing based counseling session, yet controls are offered the questionnaires only during initial and end visit and do not receive feedback on the results of the questionnaires. Controls are allowed to visit the co-located care. After one year, participants in both groups will be asked to fill out the initial questionnaires again.

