### Study design

This is an open-label randomized controlled trial with a behavioural intervention to stimulate help seeking behaviour for mental health and addiction problems among MSM who show high risk behaviour for STI and HIV at the STI clinic of Amsterdam (Fig. 1). Participants will be assigned by block randomization in groups of 4, 6 or 8, with the help of a computer program.

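### The first syndemic questionnaires are e-mailed after open-label randomisation, so initial scores and completion may depend on the arm; secondary and descriptive self-report is exposed, the primary comparison is not directly

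*Protocol article*

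**What the plan says.** Under Study intervention, allocation follows consent at once, and the next sentence sets the timing of the first measurement: "informed consent is obtained, participants will be randomized either to the intervention or the control group. After intake, and at the final visit". It is at these two points that every man completes the syndemic set. Delivery is remote: "Questionnaires will be sent via email and represent various syndemic domains". The set covers sexual compulsivity, alcohol and drug use, anxiety, depression, ADHD, alexithymia, partner violence, childhood sexual abuse and discrimination (Table 1).

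Study design states that "This is an open-label randomized controlled trial with a behavioural intervention to stimulate help seeking behaviour".

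The scores have different consequences in the two arms. For intervention men, "During these subsequent visit the outcome of all questionnaires will be discussed to provide the participant in the intervention group a better insight" into problems that may contribute to risk, and referral follows if help is accepted. Controls "do not receive feedback on the results of the questionnaires". Both arms repeat the initial questionnaires after one year.

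Under Statistical analysis, baseline characteristics and questionnaire scores are to be described and the two groups' characteristics tested against each other. The primary model is a univariable logistic regression of help seeking on arm. Changes over time are listed for drug use, risk behaviour and incident STIs, using Poisson regression with allowance for repeated measurements.

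**The concern.** A baseline value is useful in a randomised trial because allocation cannot have influenced it. Here the first self-report is collected after allocation, by e-mail, on sensitive subjects. A man who knows he is in the intervention arm can expect staff to go through his answers with him; a man who knows he is a control can expect no response. The first may hold back, or may disclose more because he hopes for help. The second may answer freely, or may not bother to return the set.

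If so, a difference in initial scores between arms could be chance imbalance or an effect of allocation, and the planned tests cannot tell the two apart. A change measured from such a starting value mixes real change with a reporting difference at the start. Groups defined by a high initial score could contain differently selected men in the two arms.

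**Working it through.** **Order of steps.** The protocol article supports this sequence:

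1. Explanation and consent (Study intervention).
2. Randomisation (same sentence).
3. First questionnaires, after intake, by e-mail (next sentences).
4. In the intervention arm only, a second set before the next three-monthly visit and discussion of all results there.
5. The same questionnaires in both arms at one year.

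No section places the first set before step 2. The later remark that controls get the questionnaires at the initial and end visit is looser, but does not reverse the order.

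**Does the plan deal with it elsewhere?** Limitations recognises open-label bias in the study team's evaluation and answers that the questionnaires are self-administered. That protects against staff influence. It does nothing about a participant's own knowledge of his arm. The reliance on computer-assisted self-interviewing under Strengths leaves the same gap.

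**Does the sample size depend on it?** No. With pooled variance and two-sided alpha 0.05 (assumed, as alpha is not stated), p1 = 0.07, p2 = 0.25, mean 0.16:

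n = [1.96 × √(2 × 0.16 × 0.84) + 0.8416 × √(0.07 × 0.93 + 0.25 × 0.75)]² / 0.18² = (1.016 + 0.423)² / 0.0324 ≈ 64 per group.

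This matches the stated 64. No baseline score enters it.

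**Which analyses use the initial scores?**

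| Analysis | Uses the initial self-report? |
|---|---|
| Primary: help seeking on arm, univariable | No |
| Incident STI, laboratory tests | No |
| Between-arm comparison of initial scores | Yes |
| Change in self-reported drug use or risk behaviour | Only if the starting value is collected in this set; not stated |
| Determinants in the multivariable Poisson models | Only if initial scores are entered; not stated |
| Results among men with high scores (mentioned in the Discussion) | Yes, if grouped by initial score; not in Statistical analysis |

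**Illustrative size (assumptions, not estimates).** The documents give no under-reporting or completion rate. Take 150 / 2 = 75 per arm and the plan's expectation that about 50% exceed at least one cut-off. Suppose a fraction f of the truly positive men in one arm under-report.

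- f = 1/10: 0.50 × 0.9 = 45% against 50%; z = 0.05 / √[(0.45 × 0.55 + 0.50 × 0.50) / 75] = 0.6.
- f = 1/5: 0.50 × 0.8 = 40% against 50%; z = 0.10 / √[(0.40 × 0.60 + 0.50 × 0.50) / 75] = 1.2.

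The sign depends on which arm under-reports. Gaps of this size would usually not reach significance, so an unremarkable baseline table would not be reassuring.

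For completion, with the same 75 per arm and either arm as the lower one:

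| Assumed completion | Initial sets returned | z |
|---|---|---|
| 95% v 90% | about 71 v 68 | 1.2 |
| 90% v 80% | about 68 v 60 | 1.7 |
| 95% v 80% | about 71 v 60 | 2.9 |

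**The case against.** The strongest reply is that the mechanism is inferred. The text says when men are randomised, not when they learn the result; intake is not defined, and the design figure is not available here. A reader might take it as fact that men answer knowing their arm. The documents do not say so. They make it plausible, because the trial is open label and nothing delays disclosure. This part of the reply stands, and the point is conditional on it.

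Second, little of the stated analysis rests on the initial scores. A reader might infer that the primary result is biased; the univariable model contains no baseline score, so it is not directly affected. A reader might also infer that changes in all the scales are to be analysed; Statistical analysis names only drug use, risk behaviour and incident STIs, and the STIs are laboratory-tested. Nor is an analysis restricted to screen-positive men planned there, so any gain in power from such an analysis has no bearing on this point. All of this stands and narrows the harm.

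Third, a man who never returns the first set might be thought lost to the trial. He is not: help seeking can be confirmed through the co-located service or reported at the end, and STIs come from the screening visits.

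Finally, moving the questionnaires forward has a cost. That is true and is counted below. None of these replies shows that collecting the first set after allocation is sound.

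**Conclusion.** The ordering flaw is real but limited. As written, the initial self-report follows randomisation in an open-label trial in which the answers have consequences in one arm only, and the stated safeguard of self-administration does not cover participants' own knowledge of allocation. Provided men know their arm when they answer, disclosure and completion can differ by arm, in either direction and by an amount the documents do not allow one to estimate.

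The harm is confined to the comparison of initial scores between arms, to change in self-reported drug use or risk behaviour if its starting value is taken from this set, and to any analysis adjusted for or grouped by initial scores. The primary help-seeking comparison and laboratory-confirmed STI incidence are not directly biased, provided that all randomised men are analysed. The change is worth making because it is cheap and removes a bias that analysis cannot repair afterwards.

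**What to change.** Change the order to consent, submission of the initial questionnaire set, randomisation, disclosure of the arm. If randomisation must stay at the consent visit, withhold the result until the set has been submitted. If this is already the practice, say so under Study intervention and define intake relative to allocation.

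For men already randomised under the present order, report completion of the initial set by arm, keep all of them in the primary analysis whether or not they returned it, and do not treat scores collected after allocation as true baseline covariates or use them to define subgroups as though they preceded allocation.

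The change reorders existing steps and needs no new data. With e-mailed questionnaires, allocation is delayed and a further contact is needed; completion at the clinic lengthens the visit instead. Some men who consent will never be randomised. That narrows the randomised population to men who complete the set, but leaves the two arms comparable. How many would drop out here cannot be judged, because the documents give no completion rate.

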### Outcomes

#### Primary outcome

Help seeking behaviour for mental health and/or addiction problems among MSM who are at high risk for STIs and HIV. Since care is co-located, we will be able to use both confirmed help seeking behaviour and self-reported help seeking behaviour (i.e. Have you seen a health professional (family doctor, counsellor or psychologist) to get help for mental problems or problems due to substance use or sex in the last year? yes/no).

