### Sample size calculation

In the Amsterdam health monitor, 7% of the MSM respondents reported to have serious psychosocial problems [25]. Because of the lack of data, we hypothesize that 7% of the participants will already be in care for psychosocial problems. With our intervention we intend to increase help seeking behaviour from 7% to at least 25%. As 89% of the MS2 cohort used at least two different drugs [2], we assume that at least 40% will score above the DUDIT or AUDIT cut-off. Combined with the other questionnaires, including the ADHD, sexual compulsivity, alexithymia, anxiety and depression questionnaires, we expect that about 50% of the study population will score above the cut off of at least one syndemic domain questionnaires. Previous studies have shown that MSM at the STI clinic are willing to participate in STI clinic initiatives. Using the opting-out strategy for HIV-testing, refusals to test for HIV dropped from 38% to 2% within one year [26]. In the syn.bas.in study we will actively stimulate help seeking behaviour. Therefore we believe that an improvement in help seeking behaviour from 7% to at least 25% is a realistic estimate. To detect an increase of help seeking behaviour from 7% to 25% and a statistical power of at least 80%, at least 64 participants per group are needed. Taking into account 10% loss to follow up, at least 141 participants are needed. Our aim is therefore to recruit 150 participants.

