### Limitations

The trial may have some limitations. First, this is an open label trial and thus the study team can be influenced in its evaluation of the outcomes resulting in information bias and an overestimation of the effect of the intervention. We cannot control for this bias. However, most questionnaires used to assess the outcome measures are validated, will be self administered and therefore cannot be influenced by the study team. Second, co-located mental health and addiction care will not only be available to participants in the intervention group, but also for participants in the control group as it seems unethical not giving them this opportunity. This may result in weakening of the contrast and thus an underestimation of the effect of the intervention. However, participants in the control group will not be stimulated by the study team. Third, the study is only performed in one center. In the future, it would strengthen our research and our findings if this study is performed in more centers and countries. Also it would strengthen the syndemic theory if we would use STI as primary outcome. As treatment for psychosocial problems can take a long time and therefore the effect on STI incidence as well, we decided to use help seeking behaviour as our primary outcome and STI as secondary outcome.

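### The self-reported primary outcome does not exclude the trial's own counselling contacts, so men who took up no care could count as help seekers, possibly more often in the intervention arm

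*Protocol article*

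**What the plan says.** The Primary outcome section gives two sources. Because care is co-located, "we will be able to use both confirmed help seeking behaviour and self-reported help seeking behaviour". The self-report item is a single yes/no question: "Have you seen a health professional (family doctor, counsellor or psychologist) to get help for mental problems", continuing to problems due to substance use or sex, over the last year. No contact is excluded.

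Under Study intervention, both arms receive motivational-interviewing counselling as standard care. In the intervention arm, study healthcare providers trained by mental health professionals also discuss the results of all questionnaires at a follow-up visit: "Via feedback and motivational interviewing the willingness to seek help will be evoked and monitored". Table 1 shows that these questionnaires cover sexual compulsivity, alcohol and drugs, anxiety, depression, ADHD and alexithymia. Controls get no feedback on their results, though they may use the co-located care.

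Under Secondary outcomes, the place where help was obtained is recorded, but this is not linked to the primary definition. The Limitations section admits that the open-label design may cause information bias and overestimation. It then offers as reassurance that most outcome questionnaires are validated and "will be self administered and therefore cannot be influenced by the study team".

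**The concern.** The item asks whether the man saw a professional, such as a counsellor, about mental, substance or sex problems. In the intervention arm, a trained provider sits down with him and discusses his scores on those subjects. A man who declined every referral could then answer 'yes' in good faith.

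Controls also receive counselling and could misattribute too. However, the content that most resembles the item is the randomised difference between the arms, so exposure to the confusing contact differs by design. If misattribution is more frequent in the intervention arm, part of the measured effect is the intervention being delivered and not care being taken up. If it is equally frequent, a real effect is harder to see.

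**Working it through.** **The plan's own figure.** Inputs from Sample size calculation: control rate 7% ("we hypothesize that 7% of the participants will already be in care for psychosocial problems"), target 25%, power at least 80%, and "at least 64 participants per group are needed". The significance level is not stated; two-sided 5% is assumed, with equal groups. With pooled p = (0.07 + 0.25)/2 = 0.16:

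n = [1.960·√(2·0.16·0.84) + 0.842·√(0.07·0.93 + 0.25·0.75)]² / 0.18² = 63.9, so 64 per group.

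The stated size reproduces and is not in question.

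**Model for misattribution.** Let the true rate be 7% in both arms, so there is no effect. Let f be the share of intervention men not otherwise in care who answer 'yes' because of trial counselling, and g the same share among controls. Then:

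- intervention rate as measured = 0.07 + 0.93·f
- control rate as measured = 0.07 + 0.93·g

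The protocol gives no value for f or g; those below are assumptions chosen to show the range. Evaluable men per arm: 150 × 0.9 / 2 = 67.5, taken as 67. The chance of a false benefit is the exact binomial probability that the two-sided 5% Pearson test is significant in favour of the intervention.

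| f | g | Intervention | Control | False benefit |
|---|---|---|---|---|
| 0% | 0% | 7.0% | 7.0% | 2.5% |
| 5% | 0% | 11.7% | 7.0% | 15% |
| 10% | 0% | 16.3% | 7.0% | 39% |
| 15% | 0% | 21.0% | 7.0% | 66% |
| 10% | 5% | 16.3% | 11.7% | 11% |
| 15% | 5% | 21.0% | 11.7% | 30% |
| 20% | 10% | 25.6% | 16.3% | 26% |
| 10% | 10% | 16.3% | 16.3% | about 2.5% |

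With g = 0, the full planned contrast appears without any real effect when f = 0.18/0.93 = 19.4%.

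**Equal misattribution with a real effect.** Take true rates of 7% and 25%, f = g = 10%, and 64 per arm. The measured rates are 0.07 + 0.93·0.10 = 16.3% and 0.25 + 0.75·0.10 = 32.5%, a difference of 16.2 points. The pooled rate is 24.4%. The standard error under the null is √(2·0.244·0.756/64) = 0.0759, and under the alternative √[(0.163·0.837 + 0.325·0.675)/64] = 0.0746. Power = Φ[(0.162 − 1.96·0.0759)/0.0746] = Φ(0.18), about 57% instead of 80%.

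**The case against.** The item has a purpose clause: the contact must have been to get help. It lists family doctor, counsellor and psychologist, not STI-clinic staff. The intervention text separates the discussion, which encourages help seeking, from the help itself, which follows by referral. Many men will read it that way. The same item and sources apply to both arms, both arms are counselled, and no misattribution rate is available. The rows with g = 0 are therefore the extreme case. All of this stands, and it limits the point to what can happen. It does not remove the ambiguity, because nothing in the item tells a man that study sessions do not count.

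The Limitations section already concedes overestimation, and the place-of-help data could allow a correction at analysis. Both are true. But the concession names influence on the study team's evaluation, not trial contacts counted as events, and the primary definition does not use the place-of-help data.

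A reader might also infer that the confirmed source favours the intervention arm because it detects only the service to which those men are steered. The protocol does not support that as a finding. Confirmation does appear to be limited to the co-located service, but controls may use it and the Abstract says all participants can be referred there. Nothing shows where controls seek help, the self-report item covers outside providers, and greater on-site use after referral is partly the intended effect. How the two sources combine is not stated, and an article may leave that to the full protocol.

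**Conclusion.** The point holds as a risk of misclassification built into the printed item. Trial counselling can be counted as help seeking, and the intervention arm receives more of the counselling that resembles the item. The direction and size depend on two unknown rates. Across the unequal rates examined, the chance of a false benefit runs from 11% to 66% against a nominal 2.5%, assuming a true 7% in both arms and 67 men per arm. Equal rates produce no false signal, but at 10% in each arm power falls to about 57%.

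It would be too strong to say that the outcome is ascertained unequally, or that a positive result would merely reflect delivery of the intervention; the protocol establishes neither. Self-administration is no safeguard here. It keeps staff from filling in the answer, but not from being the contact the man reports. The primary item is also a single question for which the article cites no validation.

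**What to change.** - Add to the item, in identical form in both arms: 'other than your STI-clinic and study visits'. State alongside it that intakes with the co-located mental-health or addiction services still count. They take place at the STI clinic, so a bare exclusion would remove genuine events.
- Use the place-of-help information already planned to remove from the primary outcome any contact that was only with study or STI-clinic staff.
- State one rule for combining confirmed and self-reported help, apply it identically in both arms, and report each source separately. Note that confirmation appears to cover only the co-located service. The confirmed record should be kept: resting the primary outcome on self-report alone would set aside the only objective source.
- Amend Limitations to say that self-administration does not remove this bias.

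The cost is a clause in one question and a few sentences of definition, with no extra participants or procedures. Observed help-seeking rates may be somewhat lower.

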#### Secondary outcomes

STI incidence and changes in risky sexual behaviours (i.e. condom use/number of partners/ number of unsafe partners/amount anal sex/recreational drug use/renounce to visit the STI clinic). In addition, we will monitor how care was experienced. If help seeking behaviour took place, information will be collected to know where help was obtained, and how useful the help was on a scale from 1 to 5.

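### The self-report item for the primary outcome is worded more broadly than the outcome and could pick up family-doctor visits for an STI or PEP

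*Protocol article*

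**What the plan says.** The Primary outcome section of the protocol article defines the outcome as "Help seeking behaviour for mental health and/or addiction problems among MSM who are at high risk for STIs and HIV". It then gives two sources: "we will be able to use both confirmed help seeking behaviour and self-reported help seeking behaviour". The self-report source is a single yes/no item, given in the text. It begins "Have you seen a health professional (family doctor, counsellor or psychologist) to get help for mental problems", and the full reason clause runs "to get help for mental problems or problems due to substance use or sex in the last year? yes/no".

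Other places that bear on how the item will be read:

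- Inclusion criteria: all men enter because of a recent STI or, if HIV negative, possibly a PEP treatment.
- Study intervention: all participants have three-monthly STI screening at the clinic, with treatment and contact tracing for new infections. Table 1 lists sex addiction as a domain, measured by the Sexual Compulsivity Scale.
- Secondary outcomes: for men who sought help, "information will be collected to know where help was obtained, and how useful the help was on a scale from 1 to 5".
- Sample size calculation: 7% versus 25%, power of at least 80%, 64 per group, 10% loss to follow-up, 141 in total, recruitment aim 150.

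**The concern.** The outcome covers two kinds of problem, mental health and addiction. The item covers three: mental problems, problems due to substance use, and problems due to sex. An STI is, in plain language, a problem due to sex. The family doctor is named as a qualifying professional, and a family doctor may be consulted for an STI or a PEP request as well as for depression. A respondent sees the item and not the definition behind it, so a truthful yes need not mean that psychosocial help was sought.

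Two things are at stake. One is meaning: some yes answers may not belong to the outcome. The other is power: the design rests on a control rate of only 7%, so a small number of such answers would raise that rate by a large fraction and blur the contrast between arms. Once the answers are collected, a bare yes/no gives no reason for the visit, so the fault is hard to repair later.

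**Working it through.** **1. Item against outcome.** The outcome limits the reason for seeking help to mental health or addiction. The item's reason clause has no such limit on the word *sex*, and the article states no exclusion for STI, HIV or PEP care. The item is therefore broader than the outcome in this one respect.

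**2. The plan's own figure.** Inputs from Sample size calculation: p1 = 0.07, p2 = 0.25, power 80%. The significance level is not stated; two-sided 5% is assumed. With p̄ = (p1 + p2)/2 = 0.16,

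n = [1.96·√(2p̄(1−p̄)) + 0.8416·√(p1(1−p1) + p2(1−p2))]² / (p2−p1)²

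= (1.0162 + 0.4230)² / 0.18² = 63.9, so 64 per group. This reproduces the stated 64. The total follows as 128 × 1.10 = 141, as stated.

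**3. Effect of extra yes answers.** Let f be the share of *true non-seekers* in each arm who answer yes because of STI or PEP care. The observed rate is then p + (1−p)f. The documents give no value for f, so a range is shown. Power at 64 per group is

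Φ{ [(p2−p1)·√64 − 1.96·√(2p̄(1−p̄))] / √(p1(1−p1) + p2(1−p2)) }.

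- f = 0: (1.440 − 1.016)/0.5026 = 0.843, power 80%.
- f = 5%: rates 0.07 + 0.93 × 0.05 = 0.1165 and 0.25 + 0.75 × 0.05 = 0.2875; (1.368 − 1.113)/0.5548 = 0.460, power 68%.
- f = 10%: rates 0.163 and 0.325; (1.296 − 1.190)/0.5965 = 0.177, power 57%.

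| f (assumed) | Control | Intervention | Difference (points) | Power at 64 per group | n per group for 80% |
|---|---|---|---|---|---|
| 0 | 7.0% | 25.0% | 18.0 | 80% | 64 |
| 5% | 11.7% | 28.8% | 17.1 | 68% | 86 |
| 10% | 16.3% | 32.5% | 16.2 | 57% | 110 |
| 20% | 25.6% | 40.0% | 14.4 | 41% | 166 |

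**4. Sensitivity to the definition and to n.** If f is instead a share of *all* men in each arm, added to the true rate (p + f), the difference stays at 18 points. Power still falls, because the rates move towards 50%: 71% at f = 5%, 64% at 10% and 57% at 20%. With the recruitment aim of 150 and 10% loss, about 67 men per arm remain (75 × 0.9 = 67.5). Power at f = 5% of non-seekers is then 70%.

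**The case against.** The strongest reply is that *sex*, placed beside mental problems and substance use, most naturally means sex addiction. That is one of the trial's own domains, listed with the "Sexual Compulsivity Scale [15"], and leaving it out would miss help seeking the trial wants to count. That is probably the intent, and it stands as a reading of the authors. It does not bind respondents, who see only the item.

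Second, these men receive STI care at the clinic, and clinic staff are not among the three named professionals. This narrows the route to STI or PEP visits to a family doctor, or to men who read the parenthesis as examples. It does not close it, since the family doctor is named.

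Third, there is a second source (confirmed help seeking in the co-located care), and the place of help is recorded. Both could help to sort answers. But help from a family doctor lies outside the co-located care, and place alone does not separate a family-doctor visit for depression from one for chlamydia. How the two sources are combined may be set out in the full protocol or the SAP, and its absence here is not held against the article.

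Three stronger readings are tempting and not supported:

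- A reader might infer that an ordinary STI consultation *does* count as an outcome event. No rule in the article says so; the wording only permits it.
- A reader might take the Background statement that "in 25% of each visit a new STI was found" with four screenings a year, compute 1 − 0.75⁴ = 68% of men with an STI in a year, and treat that as a guide to f. The figure describes infections found at clinic visits, the sum assumes independent visits, and it says nothing about family-doctor visits or answers to this item.
- A reader might object that addiction services, to which men may be referred ("participants will be referred to a relevant mental health or addiction treatment service"), are missing from the item. The item asks about substance use, counsellor can cover addiction staff, and co-located visits can be confirmed directly, so little is lost.

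**Conclusion.** The item is worded more broadly than the outcome it measures, and a truthful yes for family-doctor care of an STI or PEP is possible. That much rests on the text alone.

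The size is conditional. If 5% to 10% of true non-seekers in each arm answered this way, power at 64 per group would be about 68% to 57% instead of 80%, and the observed difference 17.1 to 16.2 points instead of 18. This assumes a two-sided 5% test, equal error in both arms, and values of f for which the documents offer no evidence; the true value may be near zero.

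It would go too far to say that the trial does not measure what it claims, or that its result would be spurious. Equal misclassification weakens a real effect and cannot produce a false one. The point is a wording fault in the primary outcome item that is worth correcting before data are collected.

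**What to change.** Reword the item, identically at the start and at one year, so that it asks about help for mental health problems, alcohol or drug problems, or sexual compulsivity/sex addiction, *not counting visits for STI or HIV testing, treatment or PEP*.

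The cost is one changed questionnaire item, with no change to design, sample size or visits. The small downside is that the new wording may not match that used in earlier surveys, which would limit comparison with them.
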